
## **6. AIMS OF THE ALADIN 2 STUDY**

### ***Primary***

The primary objective of this study in the short-term (1-year) is to compare the effect of long acting somatostatin analogue (Octreotide LAR) versus placebo on total kidney volume (TKV) change (delta TKV) as assessed by spiral computed tomography (spiral CT) scan. (see paragraph 6.1.1). While in the Long-term (3-years) the objective will be to compare the effect of long-acting somatostatin analogue (Octreotide LAR) vs. placebo on the rate of GFR decline as assessed by serial measurements of the iothexol plasma clearance.

## **Secondary**

The secondary objectives of this study is to compare, among the two groups, absolute and relative changes in renal and liver volume parameters (at month 0, 12 and 36) as well as in functional and biochemical parameters by quarterly clinical visits during the 36 month follow-up and To assess the safety profile of the somatostatin analogue.

### **6.1 Description of ALADIN 2 study**

ALADIN 2 is a randomized clinical trial coordinated by the IRCCS - Mario Negri Institute for Pharmacological Research at the Clinical Research Center for Rare Diseases, Ranica (Bergamo, Italy). Since October 2011 the above mentioned study has been recruiting patients with non diabetic chronic kidney disease.

## **7. PARITY 2 - STUDY DESIGN AND PATIENTS**

### **7.1 Enrolment plan**

The Phase A of the study has an observational, cross-sectional design. Patients are identified among the subjects referring to the Clinical Research Center for Rare Diseases *Aldo e Cele Daccò* of the IRCCS - Mario Negri Institute for Pharmacological Research fulfilling the inclusion/exclusion criteria. They will be asked to fill in the QoL Questionnaire (QoL SF-36 V1TM) and the Health and Labour Questionnaire (SF-HLQ). Data will be collected in an ad-hoc form and in parallel clinical and demographic data on the above subjects will be collected in the trial Case Report Form (CRF) of the ALADIN 2 study. At least 80 all consecutive patients will be selected after randomization.

The Phase B of the study has an observational, prospective cohort design. Patients will be asked to fill in the questionnaires yearly (SF-36 V1TM, only) and at the final study visit (both, SF-36 V1TM and SF-HLQ). Data will be collected in an ad-hoc form and in parallel clinical and demographic data of the above subjects will be collected on the trial linked CRF of the ALADIN 2 study.

Eligible patients can be identified among the subjects attending the Day Hospital of the Clinical Research Center for Rare Diseases *Aldo e Cele Daccò* of the IRCCS - Mario Negri Institute, who are enrolled in the above mentioned ongoing clinical trial in patients with non diabetic chronic kidney disease.

### **7.2 Study population**

#### **7.2.1 Number of patients**

Due to the exploratory nature of the study a formal sample size assessment is not foreseen. However at least 80 patients with non diabetic chronic kidney disease will be adequate to provide a reliable measure of the eight QoL domains (1. physical functioning, 2. role-physical, 3. bodily pain, 4. general health, 5. vitality, 6. social functioning, 7. role-emotional, 8. mental health). The above sample size has been considered adequate also to provide a reliable measure of the societal and labour costs in the above kind of participants. A difference of 5 points or more is considered as clinically significant.

#### **7.2.2 Inclusion criteria**

The following inclusion criteria will be considered:

a) patients with non diabetic chronic kidney disease;

- b) enrolled in ALADIN 2 clinical trial at the Clinical Research Center for Rare Diseases *Aldo e Cele Daccò* of the IRCCS - Mario Negri Institute for Pharmacological Research;
- c) legal capacity to give informed consent;
- d) written informed consent;
- e) inability to compile the questionnaires for different reasons from those listed in the exclusion criteria (e.g. blindness). In this case the subject will be assisted by accompanying person.
- f) Age > 18 years
- g) Clinical and ultrasound diagnosis of ADPKD
- h) Estimated GFR between 15 and 40 ml/min/1.73m^2 (by the MDRD 4 variable equation)

### 7.2.3 Exclusion criteria

The following exclusion criteria will be considered:

- a) patients with diabetic chronic kidney disease;
- b) legal incapacity and/or the circumstances rendering the patient unable to understand the nature and the scope of the study.
- c) 24-h Urinary protein excretion rate >3g (suggestive of a concomitant glomerular disease that could benefit of specific therapy)
- d) Symptomatic urinary tract lithiasis or obstruction
- e) Uncontrolled diabetes mellitus (HbA1c >8%) or hypertension (systolic/diastolic BP >180/110 mmHg)
- f) Current urinary tract infection
- g) Symptomatic biliary tract lithiasis
- h) Active cancer
- i) Psychiatric disorders or any condition that might prevent full comprehension of the purposes and risks of the study
- l) Pregnancy, lactation or child bearing potential and ineffective contraception (estrogen therapy in post menopausal women should not be stopped)

### 7.3 Setting

Day Hospital of the Clinical Research Center for Rare Diseases *Aldo e Cele Daccò* of the IRCCS - Mario Negri Institute for Pharmacological Research.

### 7.4 Study Type

The Phase A of the study is an observational cross-sectional study. The phase B has an observational, prospective cohort design.

Patient satisfying the inclusion/exclusion criteria will be provided with two questionnaires. Patient will be asked to fill in the informed consent and then the questionnaires. They will be assisted, if required, by an accompanying persons. Questionnaires will be rendered anonymous for data processing.

The recruitment is expected to start in June 2013 and to end December 2014 for Phase A. Yearly, for phase B patients will be asked to fill in the questionnaire SF-36 V1TM in order to evaluate changes in QoL; at clinical study closure, patients will be asked to fill in both questionnaires SF-36 V1TM and SF-HLQ to assess changes in QoL and societal costs. In parallel to data-gathering by two previously mentioned questionnaires, demographic and clinical data will be collected in the CRF of the linked clinical trial.

### 7.5 Quality of life and societal cost evaluation

The primary aim of this study is to assess the QoL and the societal costs as described in the following.

### **7.5.1 Quality of life**

The QoL (including physical functioning, role-physical, bodily pain, general health, vitality, social functioning, role-emotional and mental health) of all patients will be evaluated using the Version 1 of SF-36 (QoL SF-36 V1™ Questionnaire) adjusted and validated in Italy (see Enclosure A). For the Phase B of the study quantity and quality of life can be quantified by the quality-adjusted life year (QALY) indicator to be used to assess the impact of healthcare intervention on an individual patient.

### **7.5.2 Social costs**

Social costs include production losses due to the absence from work, reduced productivity, and reduced unpaid labour participation. Production losses of paid and unpaid labour will be assessed by means of the Short-Form-Health and Labour Questionnaire (SF-HLQ), of which existing translations are available for Italy (see Enclosure B). The SF-HLQ Questionnaire allows to estimate indirect non-medical costs of productivity losses caused by absence from work due to health problems. Indirect costs are used in pharmacoeconomic research to perform an economic evaluation from societal perspective.

### **7.5.3 Currency**

Euro will be considered as currency for the evaluation of social costs.

## **7.6 Sample size and statistical analysis**

### **7.6.1 Sample size**

See paragraph 7.2.1

### **7.6.2 Statistical analysis**

As distributions of QoL scores are skewed, the nonparametric Wilcoxon rank sum test will be applied. Scores will be expressed as a median and interquartile range. To compare the costs by clinical category, a multiple linear regression model will be used. Explorative analyses in pre-defined subgroups of patients (e.g. by gender) will be performed. Study results will be reported according to suggested guidelines. A *P value* less than 0.05 (two tailed) will be considered to indicate statistical significance. All analyses will be carried out using SAS 9.1 (SAS Institute Inc., Cary, NC) and Stata 12 (StataCorp LP, College Station, Texas).

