**INTRODUCTION**

---

This study is a multi-centre, prospective, randomised double-blind parallel-group comparison of long acting somatostatin analogue (Octreotide LAR) and placebo.

The study is coordinated by the Clinical Research Center for Rare Diseases of the Mario Negri Institute for Pharmacological Research, Ranica, Bergamo and will be conducted with the cooperation of:

- Hospital '*Ospedale San Giovanni di Dio*', Agrigento, Italy;
- Clinical Research Center for Rare Diseases '*Aldo e Cele Daccò*', Ranica (Bergamo), Italy
- Hospital '*Ospedale Vito Fazzi*', Lecce, Italy
- Hospital '*Ospedale Maggiore Policlinico, Mangiagalli e Regina Elena*', Milan, Italy
- University '*Università Federico II*', Naples, Italy
- Hospital '*Ospedale Ca' Foncello*', Treviso, Italy

Eligible patients will be stratified for the presence (YES or NO) of concomitant clinical conditions that could appreciably affect the rate of renal function loss over time including diabetes mellitus, 24 hour urinary protein excretion >1g, or any other evidence of concomitant renal disease without indication for specific therapy. Within each stratum patients will be randomized on a 1:1 basis to Long-acting Somatostatin (Octreotide LAR) 40 mg (treatment group) or saline solution (placebo group). Data will be collected by means of an *ad-hoc* study Case Report Form (see Appendix 1).

The general aim of the trial is to assess the efficacy of one year treatment with long-acting somatostatin analogue (Octreotide LAR) compared with placebo in slowing kidney and liver growth rate in patients with ADPKD and moderate/severe renal insufficiency (estimated GFR by MDRD 4 variables: 15-40 ml/min/1.73m^2) and to assess whether and to which extent this translates into slower renal function decline over 3-year follow-up.

Primary objectives are the followings: to compare the effect of long acting somatostatin analogue (Octreotide LAR) versus placebo on total kidney volume (TKV) change (delta TKV) as assessed by spiral computed tomography (spiral CT)

scan (short-term, one year) and to compare the effect of long-acting somatostatin analogue (Octreotide LAR) vs. placebo on the rate of GFR decline as assessed by serial measurements of the iohexol plasma clearance (long-term, three years).

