The secondary objectives are to compare, among the two groups, absolute and relative changes in renal and liver volume parameters (at month 0, 12 and 36) as well as in functional and biochemical parameters by quarterly clinical visits during the 36 month follow-up. In particular, the following parameters will be assessed:

- Total kidney volume (at 3-years)
- Total renal cyst volume\*
- Total renal parenchyma volume\*
- Total renal intermediate volume\*
- Total liver and liver cyst volumes\*

*\*When feasible, by minimized radio contrast agent administration during CT acquisition*

- GFR decline (as assessed by serial measurements of the plasma iohexol clearance at month 0 and, every 6 months thereafter)
- Slope of eGFR (by MDRD 4 variable equation)
- Progression to the combined end point of doubling of serum creatinine and/or ESRD (*ESRD: need for chronic renal replacement therapy by dialysis or transplantation established on the basis of standard clinical criteria*)
- Progression to ESRD considered as a single endpoint
- Systolic, diastolic and mean blood pressure
- 24 h urinary protein excretion rate (at month 0 and every six months thereafter)
- Urinary osmolality (assessed from urine sodium, urea and glucose concentration on 24 hr urine samples)
- Morning spot urine sample (proteins, albumin, creatinine)
- Serum Insulin Growth Factor-1 (IGF-I)
- 24 h urinary phosphorus, creatinine and creatinine clearance
- Gallbladder sand/stones and renal stones (by ultrasonography).

In a subgroup of patients referred to the Clinical Research Center for Rare Diseases 'Aldo e Cele Daccò' and/or other institutions where these evaluations are feasible the

following other secondary objectives are to compare, among the two groups the quality of life and the societal costs by submitting to consenting patients a *Quality of life (QoL) Questionnaire* - Version 1 of SF-36 (QoL SF-36 V1™ Questionnaire) validated in Italy – and a *Short-Form-Health and Labour Questionnaire (SFHLQ)*. (See Appendix 2).

Furthermore, for exploratory purposes only, the treatment effect on endothelin and MCP-1 urinary excretion rate (overnight urine sample), in a subgroup (pending on study findings and fund availability).

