**2. SYNOPSIS**

|                                      |                                                                                                                                                                                                                                                                                                                                                                                                                                                              |
|--------------------------------------|--------------------------------------------------------------------------------------------------------------------------------------------------------------------------------------------------------------------------------------------------------------------------------------------------------------------------------------------------------------------------------------------------------------------------------------------------------------|
| TREATMENT                     | Not applicable                                                                                                                                                                                                                                                                                                                                                                                                                                               |
| TITLE                         | P A T I E N T – R E P O R T E D I N F O R M A T I O N A C C O R D I N G T O T H E T Y P E O F I N S T R U M E N T – 02 (PARITY – 02) - Quality of life and social costs in patients with non diabetic chronic kidney disease |
| OBJECTIVE                     | To assess quality of life and societal costs in patients with non diabetic chronic kidney disease enrolled in the ongoing clinical trial: ALADIN 2 conducted at the Clinical Research Center Aldo e Cele Daccò , Mario IRCCS - Negri Institute, Ranica (BG), Italy                                                                                                                                                                                    |

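### The SAP sets quality of life and societal costs as an octreotide versus placebo objective, but no analysis text names randomised arm as the contrast

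*Supplement*

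**What the plan says.** The SAP Introduction describes a 1:1 trial of octreotide LAR against placebo: "Within each stratum patients will be randomized on a 1:1 basis". For a subgroup at centres where the questionnaires are feasible, it states that the "following other secondary objectives are to compare, among the two groups the quality of life and the societal costs", using the SF-36 and the Health and Labour Questionnaire.

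The questionnaires are governed by PARITY-02, included in the same supplement. Its synopsis lists treatment as not applicable and gives the objective as: "To assess quality of life and societal costs in patients with non diabetic chronic kidney disease". On design, section 7.1 says: "The Phase A of the study has an observational, cross-sectional design". It describes Phase B as a prospective cohort. Section 7.4 has patients repeat the SF-36 yearly "in order to evaluate changes in QoL; at clinical study closure, patients will be asked to fill in both questionnaires".

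The analysis is in PARITY-02 section 7.6.2. QoL scores are to be analysed with a Wilcoxon rank-sum test, and no groups are named. On costs: "To compare the costs by clinical category, a multiple linear regression model will be used". Exploratory subgroup analyses are also planned, with gender as the example.

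**The concern.** The objective and the analysis do not meet. The objective asks whether the randomised groups differ. The cost analysis asks whether clinical categories differ, and the QoL analysis does not say what it compares.

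Two things are at stake. First, a statistician who follows the cost rule literally produces no octreotide versus placebo estimate, so the stated objective has no answer. Second, an unnamed grouping for the QoL test can be settled after the data are seen. With eight SF-36 domains and several possible groupings, that choice should be fixed beforehand.

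**Working it through.** No arithmetic on effect size applies: PARITY-02 section 7.2.1 foresees no formal sample-size calculation and gives no standard deviation or power. The check is to follow the objective through the documents.

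1. **Objective.** SAP Introduction: compare QoL and societal costs between the two randomised groups.

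2. **SAP analysis.** Section 3.3.1 covers total kidney volume and measured GFR slope. Section 3.3.2 covers vital signs, laboratory and urine measures, kidney volumes and GFR slopes. Section 3.3.3 covers ESRD, mortality and cardiovascular events. None mentions QoL or costs. The table list (Section 4), figure list (Section 5) and table templates contain no QoL or cost output. The questionnaires appear only as Appendix 2. Most other secondary parameters receive at least summaries by treatment group; these two receive nothing.

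3. **PARITY-02 analysis.** Section 7.6.2 reads as follows against the objective:
   - QoL: rank-sum test, groups not stated. Arm, gender or clinical category would all fit.
   - Costs: multiple linear regression, contrast stated as clinical category, which is not defined. Arm is not named as a term.
   - Subgroups: gender is the only example.

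4. **Rest of PARITY-02.** Sections 5 and 6 and Enclosure A mention octreotide, and sections 5 and 6 set it against placebo, but only to recount earlier work or the parent trial's own aims. The sub-study's objective, design and analysis sections do not name the arms as its comparison.

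5. **What the cost rule estimates.** As written, the model is cost = b0 + b1 × category + other terms. The objective needs cost = b0 + b1 × arm + b2 × stratum + other terms, with b1 and its confidence interval as the answer. The first model has no arm coefficient unless someone adds one.

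6. **Is there a pre-treatment score?** Section 7.1 selects patients after randomisation. Section 6.1 says ALADIN 2 has recruited since October 2011. Section 7.4 expects Phase A recruitment from June 2013, which is 3 + 12 + 5 = 20 months later. Section 9 gives a start of March 2013, which is 3 + 12 + 2 = 17 months later. On either date, a patient randomised early could complete a first questionnaire well into the 36-month follow-up. Some first scores may therefore be on-treatment values, so change from first questionnaire is not reliably change from baseline.

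**The case against.** The strongest reply is that the arm comparison is implied. The rank-sum test is for two independent groups, the SAP says the comparison is between the two groups, and a reader putting these together would naturally test octreotide against placebo. That is a fair reading for QoL and may be what was intended, but the text does not say so. It does not rescue costs, where a different contrast is stated. It is also fair that this is an exploratory objective in a subgroup.

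Three stronger readings are tempting, and the documents do not support them.

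- **That the sub-study pools the arms and tests before against after.** The cohort wording and the stated interest in changes suggest it. But no section says the arms are pooled, and no paired test is planned; the one named test is for independent groups. Error rates for a pooled before-and-after test would describe an analysis nobody has proposed.
- **That a change common to both arms will be credited to the drug.** Section 7.5.1 calls the QALY an "indicator to be used to assess the impact of healthcare intervention on an individual patient". This can be read as a general description of what a QALY is for. It says only that QALYs can be calculated, and it does not name octreotide.
- **That 80 patients are wrongly claimed to be enough for a 5-point arm difference.** Section 7.2.1 says "A difference of 5 points or more is considered as clinically significant", but it claims only that 80 gives a reliable measure of the SF-36 domains and costs. That is descriptive adequacy. The 5 points are a clinical threshold, not a powered treatment effect.

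**Conclusion.** The point holds as a mismatch between objective and analysis. For costs, the stated contrast does not serve the stated objective. For QoL, the contrast is not specified. It would be wrong to conclude that the arms will certainly not be compared; the finding is that the plan does not commit to comparing them.

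Its reach is limited to one exploratory secondary objective covering two outcomes, QoL and costs, in a subgroup. Neither primary endpoint is touched. The conclusion rests on the text alone and on no assumed variance, correlation or effect. Naming the arm is more than filling in a detail, because for costs it replaces a stated contrast. It is an improvement that costs almost nothing.

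**What to change.** In PARITY-02 section 7.6.2, with a cross-reference from SAP section 3.3.2:

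- **QoL.** Apply the rank-sum test already planned to each SF-36 domain score by randomised arm. Report a Hodges-Lehmann difference with 95% CI, the estimator SAP section 3.3.1.2 already uses for GFR slopes. State the visit at which scores are compared, and report by arm how many patients have no questionnaire at that visit.
- **Costs.** Make randomised arm the main term in the regression and include the randomisation stratum as a covariate. Define clinical category. Include it only if it comes from pre-randomisation data; if it reflects a state reached after randomisation, adjusting for it could bias the arm effect.
- **Descriptive results.** Label within-cohort changes and QALYs as descriptive, and note that first questionnaires follow randomisation and some may be completed on treatment.

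The cost is a few sentences in two documents and a few extra tables. No new data are needed. Section 7.4 says questionnaires are made anonymous for processing, so the link between patient code and randomised arm must be kept for the analysis.

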## **8. DATA COLLECTION**

The scores of QoL Questionnaire SF36 V1™ and indirect costs (missed days work, etc.) will be quantified by means of the Health and Labour Questionnaire and recorded on a paper data form and coded on a Excel file (Microsoft Office Excel 2003).

## **9. STUDY START**

Expected Phase A and Phase B study are foreseen to start in March 2013.

## **10. STUDY COMPLETION**

The study will be completed depending on study closure of ALADIN 2 trial.

## 11. ACKNOWLEDGEMENTS

The authors are grateful to [name] [name] (Erasmus University Rotterdam, The Netherlands), [name] (University of Groningen, The Netherlands) and colleagues for permission to use the SF-HLQ instrument.

